### Sample Size

Power analysis was based on data from a recent study of community dwelling older people with mild balance impairment (approximately 15–25% impairment compared to healthy controls), which is in the approximate range of impairment anticipated in our sample with mild-moderate severity Alzheimer's disease. Using data from one of the main force platform measures of balance (Limits of Stability, Maximum Excursion, mean score 71.9; SD 14.3) and a clinical balance measure (Step Test, mean score 14, SD 3.6), power calculations were performed to determine the required sample size to demonstrate a 10% improvement, at 80% power and alpha = 0.05. Using these two tests as primary outcome measures for evaluating the effectiveness of the balance retraining exercise programme, a sample size of 80 per group will be required (160 overall). Assuming a loss to follow up of 25%, a sample of 214 will be required for the main study (RCT study). For the longitudinal sub-study, based on the estimated magnitude of balance impairment (15–25%) relative to healthy age matched controls from previous studies, a sample size of 42 will be sufficient to demonstrate group differences (healthy vs Alzheimer's disease group) on the Limits of Stability Maximum Excursion outcome. Allowing for 20% dropout in this group/year over the 2 year follow-up period for this group, 64 healthy age and gender matched controls (matched to the first 64 participants in the control group) will be required for the longitudinal follow-up component of the study. This sample size will be sufficient to identify significant decline in performance over a two year follow-up period (power 0.8, alpha 0.05, single sided analysis, assuming 7% decline in balance performance/year in the Alzheimer's disease group). Previous studies have shown a change of 1–2% per year on balance and mobility measures for healthy older people [58], and over 10% decline in Activities of Daily Living (including locomotion) in six months in people with moderate severity dementia [59].

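### At 80 per group the Step Test has about 69% power, not the stated 80%, on a simple two-sided comparison; the figure fits that primary outcome only one-sided, and the protocol does not state sidedness for the RCT

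*Protocol article*

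**What the plan says.** The Sample Size section takes its inputs from an earlier study of community-dwelling older people: "Limits of Stability, Maximum Excursion, mean score 71.9; SD 14.3" and "Step Test, mean score 14, SD 3.6". The RCT is sized "to demonstrate a 10% improvement, at 80% power and alpha = 0.05". Using both measures as primary outcomes, the protocol concludes that "a sample size of 80 per group will be required (160 overall"), and then: "Assuming a loss to follow up of 25%, a sample of 214 will be required for the main study".

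No sidedness is given for the RCT. Later in the same section, in the sentence on decline in the longitudinal sub-study, the protocol does give one: "power 0.8, alpha 0.05, single sided analysis, assuming 7% decline in balance performance/year".

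The Primary Outcome Measures section names LOS Maximum Excursion and the Step Test as the two primary outcomes. The Statistical Analysis section plans repeated measures ANOVA between the two groups. The covariates are whichever variables turn out to differ at baseline. No within-person correlation is given.

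**The concern.** One sample size and one power figure are offered for two outcomes with different standardised effects. A 10% improvement is about 0.50 SD on LOS but only about 0.39 SD on the Step Test, so a size that is ample for the first may be short for the second. If the stated 80% is to cover both primary outcomes, it must hold for the Step Test.

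At stake is how a Step Test result is read. On a simple two-sided comparison, a true 10% benefit would be missed about 31% of the time (1 − 0.686), where the protocol implies 20%. A reader relying on the stated 80% would give a null Step Test result more weight than it deserves.

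**Working it through.** **Inputs (protocol article, Sample Size).** LOS mean 71.9, SD 14.3. Step Test mean 14, SD 3.6. Improvement 10%, power 80%, alpha 0.05, equal groups, 80 evaluable per group, 25% loss.

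**Standardised effects.**
- LOS: 0.10 × 71.9 = 7.19, and 7.19/14.3 = 0.503.
- Step Test: 0.10 × 14 = 1.4, and 1.4/3.6 = 0.389.

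**Loss to follow-up.** 160/0.75 = 213.3, so 214. This step reproduces.

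**Size per group.** The normal approximation is n = 2(z_alpha + z_power)²/d², where z_power = 0.842 and z_alpha = 1.960 (two-sided) or 1.645 (one-sided). The t-based results use the noncentral t distribution.
- Step Test, two-sided: 2 × (1.960 + 0.842)²/0.389² gives 104 (t-based 105).
- Step Test, one-sided: 2 × (1.645 + 0.842)²/0.389² gives 82 (t-based 83).

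| Outcome | Test at 0.05 | n per group for 80% power (normal / t) | Power at 80 per group (normal / t) |
|---|---|---|---|
| LOS | two-sided | 63 / 64 | 88.9% / 88.5% |
| LOS | one-sided | 49 / 50 | 93.8% / 93.6% |
| Step Test | two-sided | 104 / 105 | 69.1% / 68.6% |
| Step Test | one-sided | 82 / 83 | 79.2% / 78.9% |

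For a single outcome, the stated 80 is approached only by the Step Test at one-sided 0.05.

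**Detectable difference.** At 80 per group, two-sided 0.05 and 80% power, the detectable effect is 0.446 SD (t-based). On the Step Test that is 0.446 × 3.6 = 1.60 steps, and 1.60/14 = 11.5%.

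**Rounding.** Letting the Step Test mean run from 13.5 to 14.49 and the SD from 3.55 to 3.65 keeps two-sided power between about 64% and 73%. Rounded inputs do not explain the gap.

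**Dependence on the analysis.** The figures above are for an unadjusted comparison at one time point. The protocol gives no baseline to 6-month correlation r, so the values below are assumptions. Adjusting for the baseline outcome (ANCOVA) multiplies the variance by 1 − r². Analysing change from baseline multiplies it by 2(1 − r). Two-sided Step Test power at 80 per group, t-based:

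| Assumed r | Change from baseline | Baseline-adjusted (ANCOVA) |
|---|---|---|
| 0.3 | 54% | 73% |
| 0.5 | 69% | 81% |
| 0.6 | 78% | 86% |
| 0.7 | 88% | 93% |

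**The case against.** The strongest reply is that 80 is not an arithmetic error. The RCT sentence gives alpha without sidedness and its aim is directional. The same section uses a single-sided analysis for the sub-study. At one-sided 0.05 the more demanding outcome needs 82 to 83 per group, close to 80. A reader might infer from the 69% that the protocol's own figures prove the stated power wrong. The documents do not support that much, because the two-sided test is an added assumption. It is still the more natural reading. The protocol names a single-sided test where it uses one and does not do so for the RCT, and an ANOVA F test is ordinarily non-directional. A one-sided size would then not match the planned test.

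The second reply is that an unadjusted comparison at one time is not the planned analysis. This stands. Power under repeated measures ANOVA depends on a correlation that is not given, and could be above or below 69%. So 69% should not be read as the established power of this trial. Nor does the planned analysis clearly close the gap: on a change contrast, power reaches 80% only at r of about 0.62, and the section does not commit to adjusting for the baseline outcome.

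It could also be said that 80 arose in some other way. Averaging the two standardised effects, (0.503 + 0.389)/2 = 0.446, does give 80 per group two-sided. The protocol does not mention this, and it would leave the Step Test at about 69%.

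**Conclusion.** The point holds in a conditional form. If the RCT is tested two-sided at 0.05, 80 per group gives about 89% power for LOS and about 69% for the Step Test on a simple comparison of means, so the stated 80% fails for one of the two primary outcomes. If it is tested one-sided, the figure is roughly right (about 79% for the Step Test), but the protocol neither says so nor plans a test that matches. On either reading the Sample Size section needs correcting.

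This rests on the protocol's means and SDs, equal groups and no covariate adjustment. LOS exceeds 80% on either sidedness. A reader might go further and ask for the power to succeed on both outcomes. The protocol names two primary outcomes but does not require success on both, so that figure has no bearing here.

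**What to change.** Keep the 214 participants and amend the Sample Size section:

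1. State whether the RCT tests are one- or two-sided.
2. If two-sided, give power separately for each outcome: about 89% for LOS and about 69% for the Step Test at a 10% improvement, unadjusted. Equivalently for the Step Test, 80% power for a difference of about 1.6 steps (11.5%).
3. If one-sided, declare and justify it, and replace the non-directional F test in the Statistical Analysis section with a matching directional test.

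This costs wording only and makes one stated figure less favourable.

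Optionally, change the Statistical Analysis section so that each primary outcome is adjusted for its own baseline value, which is already collected, and base the power statement on that analysis. Step Test power at 80 per group, two-sided, would then be about 73%, 81%, 86% or 93% for an assumed correlation of 0.3, 0.5, 0.6 or 0.7. These figures may be quoted only if the analysis itself is changed, and the assumed correlation should be stated with its source. This option amends the planned analysis as well as the wording, but needs no extra patients or measurements.

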### Missing data

To evaluate participant dropout bias, testing for missing at random (MAR) data will be performed. If the missing values are missing at random, the procedures of maximum likelihood (ML) [60] and multiple imputation (MI) [61] will be used for intention-to-treat analyses. In addition, the results from these two intention-to-treat analysis will be compared, as well as the results analyzed with dropped data to determine what difference the three approaches may cause.

## Discussion

Considerable research evidence exists to suggest that a range of single and multiple falls prevention interventions may reduce falls in the community setting [25,62], and exercise is considered to be an effective and essential part of fall prevention programmes [22,23]. In addition, a recent meta-analysis of almost 50 randomised trials investigating exercise interventions to reduce falls in older people has concluded that a focus on balance and lower muscle strength training are key contributing factors to the success of exercise interventions [24]. Despite cognitive impairment being an independent risk factor for falls, most community-based falls prevention studies have excluded participants with cognitive impairments such as Alzheimer's disease. In the few studies that have included participants with Alzheimer's disease, the focus has been on problems of balance impairment, falls and falls injuries at later stages of disease progression, or among those with Alzheimer's disease living in residential facilities [63]. A clear gap in the current research relates to whether there is potential to implement a balance exercise programme at the earlier stages of the disease process in community dwelling people with Alzheimer's disease – particularly when these people still have capacity to safely and actively engage in this type of intervention.

Given (i) the high risk of falls associated with advanced Alzheimer's disease, (ii) the negative impact of balance problems and falls on ongoing care within the home environment, and (iii) the increased risk of hospitalisation or admission to a residential care facility after a fall, this project has the potential for wide applicability within this target group. Specifically, if it could be shown that balance can be maintained or improved at the earlier stages of Alzheimer's disease, this improved balance capacity may possibly reduce fall risks at later stages of the dementia pathway. Furthermore, from a health service perspective, if the approach in the proposed study were successful, it would support a case for balance screening and the provision of a balance training exercise programme as a routine component of early management for people diagnosed with Alzheimer's disease. Finally, delaying onset of balance dysfunction by several years may also have an effect of reducing disability-adjusted life years lost associated with Alzheimer's disease.
